**4.2 Exclusion criteria:**

(1) Cranial CT/MRI can display the presence of cerebral hemorrhage

(2) The expected survival time of patients less than three months because of complicated serious systemic diseases

(3) The patients cannot provide continuous follow-up information by investigator judgments

# 5 Treatment regimen

In the study, the doctors can select the specific treatment regimen for cerebral stroke according to the patient's clinical medical history and characteristics of symptoms as well as the China 2011 Guidelines for Diagnosis and Treatment of Ischemic Cerebral Stroke. This study has no limitations on the selection, dose and treatment course of the treatment drugs.

According toChinese Guideline for Diagnosis and Management of Acute Ischemic Stroke2010, The specific treatment on acute ischemic cerebral stroke refers to the intervention with a certain link in the pathophysiological mechanism of ischemic injuries. Examples are given to the following common drugs for illustration:

1. Intravenous thrombolysis drug: rt-PA and urokinase.
2. Anti-platelet drugs: aspirin and Clopidogrel
3. Anticoagulants: including unfractionated heparin, low molecular heparin, ateroid, oral decoagulants and thrombin inhibitor.
4. Volume expansion drug: hydroxyethyl starch, and low molecular dextran.
5. Nerve protective agents: Edaravone, nicholin and ganglioside.
6. Cerebral blood flow perfusion improving drugs: butylphthalide, human urine kininogenase (Urinary Kallidinogenase for Injection).
7. Chinese herbal medicines: Shuxuetong injection, and Danhong injection.

# 6 Concomitant treatment

Combined medications: any other drug given during the inpatient treatment except the specific treatment for acute ischemic cerebral stroke.

The cerebral infarction non-specific treatment drugs include dehydrants, antihypertensive drugs, antihyperlipemic drugs, hypoglycemic drugs, and anti-infective drugs etc.

When the patients are included into the study (namely first visit), all accompanying diseases and combined medications must be recorded in detail. At the discharge visit, it is necessary to record any change in the combined medications in detail.

For each kind of combined medications, the following information should be collected: generic name, dose, initial date, ending date or continuous use, and indications.

# 7 Study procedures

**7.1 Baseline phase**

**Visit1 (At admission Day 0)**

- Signing informed consent forms
- Verify the inclusion / exclusion criteria
- Demographic materials (Sex, Age) and medical insurance type
- Visit delay and visits accepted by emergency*

The items with a "*" can be evaluated.

- Past medical history (stroke, hypertension, diabetes, dyslipidemia, coronary heart disease, atrial fibrillation, carotid plaques, and history of tumor), the history of medications during the recent three days, and risk factors*

The items with a "*" can be evaluated.

- Onset and admissiond (Stroke occurrence time, and main symptoms)
- Imaging examination (Cranial CT/MRI and vascular examination)

If possible, the researchers are expected to burn the disks to store the patient's imaging materials (cranial CT / MRI imaging)

- Vital Signs (Body temperature, pulse, respiration and blood pressure)

The changes in body temperature 1 day and 24 hours after the onset need to be collected.

- NIHSS score
- mRS score
- EQ-5D scale
- ECG examination
- Laboratory tests (blood routine, blood glucose, blood lipids, hepatic and renal functions, cardiac enzymes, serum electrolytes, coagulation)
- Concomitant treatment
- Adverse events

**7.2 Treatment phase**

**Visit 2 (7 ± 2 days after administration)**

- Vital Signs (Body temperature, pulse, respiration and blood pressure)
- NIHSS score
- Concomitant treatment
- Adverse events

**Visit 3 (At discharge)**

- Vital Signs (Body temperature, pulse, respiration and blood pressure)
- Glasgow coma score
- TOAST classification
- NIHSS score
- mRS score
- EQ-5D scale
- ECG examination
- Laboratory tests (blood routine, blood glucose, blood lipids, hepatic and renal functions, cardiac enzymes, serum electrolytes, coagulation)
- Therapeutic regimen (namely the specific treatment of acute ischemic cerebral stroke)

The name (generic name), dose, administration method, initial medication time and medication duration of the treatment drug need to be recorded.

- Collect medical expenses

The direct medical costs are acquired through the expense detailed list when the patient is discharged, and the direct non-medical costs (including the transportation expense, nutrition expense and family accompany expenses) are acquired through the inquiry of the patient or his/her family.

The contents of the collected direct medical costs include:

1. Total inpatient expenses (including the self-paid part)
2. Category of comprehensive medical service: including general medical service expense, general treatment and procedure expense, nursing expense and other expenses
3. Category of diagnosis: including pathological diagnosis expense, laboratory diagnosis expense, imaging diagnosis expense, and clinical diagnosis expense
4. Category of treatment: including expense of non-surgical item and surgical treatment expense
5. Rehabilitation expense
6. TCM therapy expense
7. Western medicine expense
8. Category of Chinese medicines: including expense of prepared Chinese medicine and expense of Chinese herbal medicine
9. Category of blood and blood products: including expense of blood, expense of protein-like products, expense of globulin-like products, expense of blood coagulation factor like products, and expense of cytokine like products.
10. Category of consumables: including the expense of disposable medical materials for examination, the expense of disposable materials for treatment, and the expense of disposable materials for surgery
11. Other expense

- Concomitant treatment

The non-specific treatment drugs for acute cerebral infarction (dehydrants, antihypertensive drugs, antihyperlipemic drugs, hypoglycemic drugs, and anti-infective drugs etc.), supporting therapy, and drugs for the treatment of accompanying diseases.

- Adverse events

**7.3 Follow-up period**

**Visit 4(After administration 90 ± 14 days, Outpatient or telephone visit)**

- mRS score
- MMSE scale (Only applicable to the patients that receive follow-up visits at hospitals)
- EQ-5D scale
- Collect medical expenses

The patient's medical expenses from discharge to visit 4 are collected (AIS related medical expense, not including the medical expenses for other diseases), including direct medical cost (including the dug expense, examination expense, laboratory test expense, diagnosis and treatment expense, nursing expense and bed expense due to outpatient service / emergency service / hospitalization) as well as direct non-medical cost (including transportation expense, nutrition expense, family accompanying expense and the expense of auxiliary devices). The above expenses are obtained through the inquiry from the patient and (or) family. Where the expense list cannot be provided, the estimate value verbally given prevails.

- Recurrence

The patient should be inquired about the recurrence, and the date of recurrence and whether the recurrence leads to inpatient treatment should be recorded.

Note: whether the disease recurs is based on the diagnosis of the medical institution verbally told by the patient or his/her cerebral infarction.

The stroke recurrence is defined as: 1) in conformity with the diagnosis criteria of ischemic cerebral stroke; 2) the history of past stroke with clear symptom; 3) infarction foci at different periods verified by cranial CT/MRI[[13]](#bookmark15).

- Survival status

The patients should be inquired about the survival status, and as for the dead patients, it is necessary to record the date and reason of death.

- Re-admission

The patient should be asked whether he/she is re-admitted as well as the frequency and reasons of admission.

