| **Inclusion criteria** | 1. Age≥18 years 2. In conformity with the diagnosis criteria (draft) of China 2014 Guidelines for Diagnosis and Treatment of Ischemic Cerebral Stroke 3. The onset time of thrombolytic patients are within the time window of thrombolysis 4. The onset time of thrombolytic patients are within one week 5. The patients or legal guardians can understand and sign the informed consent form |
| **Exclusion criteria:** | 1. Cranial CT/MRI can display the presence of cerebral hemorrhage 2. The expected survival time of patients less than three months because of complicated serious systemic diseases i 3. the patients cannot provide continuous follow-up information by investigator judgments |
| **Primary efficacy endpoint** | The proportion of patients with good prognosis (mRS=0-2 points) at 90 days after treatment |
| **Secondary efficacy endpoint** | 1. The proportion of patients with poor prognosis (mRS= 3-5 points) and death (mRS=60 points) at 90 days after treatment 2. The changes in National Institutes of Health Stroke Scale (NIHSS) at discharge from baseline 3. The changes in EQ 5 visual analogue scale (EQ-5D, VAS) at discharge from baseline |
| **Safety parameters** | 1. Incidence rate of symptomatic intracranial hemorrhage transformation during the hospital stay 2. Adverse events 3. Vital Signs 4. Laboratory tests (blood routine test, blood glucose, blood lipids, liver and renal functions, myocardial enzymes, serum electrolytes, and coagulation function) 5. ECG examination |
| **Exploratory analysis** | Analysis on the prescriptions of acute specific treatment for different TOAST types  Stroke recurrence rate and incidence rate of post-stroke dementia at 90 days after treatment |
| **Pharmacoeconomic evaluation** | Calculate the cost/utility of the protocol of combinations of different drugs, and ascertain the optimal protocol of hospital treatment of patients with acute cerebral stroke.  As for the costs, only the direct cost is collected, and the indirect cost and implicit cost are not collected. The quality adjusted life years (QALYs) is adopted for the utility analysis as the health outcome parameter. |

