**Visit 5 (360 ± 28 days after administration, telephone visit)**

- mRS score
- EQ-5D scale
- Collect medical expenses

The patient's medical expenses from visit 4 to visit 5 should be recorded. (AIS related medical expense, not including the medical expenses for other diseases), including direct medical cost (including the dug expense, examination expense, laboratory test expense, diagnosis and treatment expense, nursing expense and bed expense due to outpatient service / emergency service / hospitalization) as well as direct non-medical cost (including transportation expense, nutrition expense, family accompanying expense and the expense of auxiliary devices). The above expenses are obtained through the inquiry from the patient and (or) family. Where the expense list cannot be provided, the estimate value verbally given prevails.

• Recurrence

The patient should be inquired about the recurrence, and the date of recurrence and whether the recurrence leads to inpatient treatment should be recorded.

Note: whether the disease recurs is based on the diagnosis of the medical institution verbally told by the patient or his/her cerebral infarction.

The stroke recurrence is defined as: 1) in conformity with the diagnosis criteria of ischemic cerebral stroke; 2) the history of past stroke with clear symptom; 3) infarction foci at different periods verified by cranial CT/MRI[13].

• Survival status

The patients should be inquired about the survival status, and as for the dead patients, it is necessary to record the date and reason of death.

• Re-admission

The patient should be asked whether he/she is re-admitted as well as the frequency and reasons of admission

- Study completed / ending page

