**8.2 Safety evaluation**

The safety indexes in this study include:

1. Incidence rate of symptomatic intracranial hemorrhage transformation during the hospital stay
2. Adverse events
3. Vital Signs
4. Laboratory tests (blood routine test, blood glucose, blood lipids, liver and renal functions, myocardial enzymes, serum electrolytes, and coagulation function)
5. ECG examination

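### The stroke recurrence endpoint admits only ischaemic, imaging-verified events yet is ascertained by verbal report, and haemorrhagic stroke after discharge has no endpoint or planned comparison of its own

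*Protocol*

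**What the plan says.** The Abstract lists as exploratory "Stroke recurrence rate and incidence rate of post-stroke dementia at 90 days after treatment". Section 8.4 gives the same three-month horizon, and section 10.6 compares recurrence between groups by chi-square or Fisher's exact test, with Bonferroni-adjusted pairwise comparisons if the overall test is significant.

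Section 7.3 defines recurrence identically at Visits 4 and 5. The first two criteria are "1) in conformity with the diagnosis criteria of ischemic cerebral stroke; 2) the history of past stroke with clear symptom"; the third is "infarction foci at different periods verified by cranial CT/MRI". The note directly above states that "whether the disease recurs is based on the diagnosis of the medical institution verbally told by the patient or his/her cerebral infarction". The last words look like a translation slip, probably for the family. At both visits the patient is also asked for the date of recurrence and whether it led to inpatient treatment.

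Visit 4 is by clinic attendance or telephone and Visit 5 by telephone. The study flow diagram schedules imaging at Visit 1 only.

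The one named haemorrhage endpoint, in section 8.2, is "Incidence rate of symptomatic intracranial hemorrhage transformation during the hospital stay". Section 10.4 compares haemorrhagic transformation between groups and describes SAE incidence for the sponsor's product.

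**The concern.** Three things do not fit together. The name covers all stroke, while the first criterion admits only ischaemic stroke. The definition requires imaging verification, while the stated source is what someone says about an outside diagnosis. The second and third criteria, taken alone, describe a person who has had more than one stroke; they do not themselves require a new event.

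What is at stake is how the section 10.6 comparison can be read. The drug classes in section 5 include thrombolytics, antiplatelets and anticoagulants, so the groups may differ in antithrombotic content. A count that includes only ischaemic events shows one side of the cerebrovascular balance. Sites could also count differently: one may accept a reported diagnosis, another may refuse it without proof of infarct foci of different ages. An SAP could choose between the rules, but it cannot recover stroke type or imaging status that was never recorded.

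**Working it through.** The protocol gives no recurrence or haemorrhage rate, and its 10,000 patients rest on no effect size, so there is no stated figure to reproduce. The check is of the text.

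**1. Name against definition.** The Abstract and section 10.6 refer to stroke. The first criterion is "in conformity with the diagnosis criteria of ischemic cerebral stroke". A new haemorrhagic stroke fails it, whatever the other criteria say.

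**2. Definition against source.** Take a patient who says by telephone that a hospital diagnosed a new cerebral infarction, with nothing known about imaging. Under the note this is a recurrence. Under the third criterion it is not established. The protocol schedules no follow-up imaging, asks for no outside report and does not say which rule prevails.

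**3. New event or history.** Prior stroke is recorded at baseline and is not an exclusion. The criteria do not mention onset after the index stroke. The 90-day horizon and the question about date of recurrence do imply it. The omission is a drafting gap.

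**4. Where a haemorrhagic stroke after discharge can appear.**

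| Route | Place | Limit |
|---|---|---|
| mRS 0-2, 3-5, death at day 90 | 8.1 | Does not identify cause; a patient who recovers to mRS 0-2 counts as a good outcome |
| AE/SAE | Flow diagram and its notes, 3, 11 | Window worded in different ways; not listed among Visit 4 or 5 procedures in 7.3 |
| Reason for death or re-admission | 7.3 | Recorded, but section 10 gives no analysis |
| Haemorrhagic transformation | 8.2, 10.4 | Endpoint stops at discharge |

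**5. Length of the AE gap.** The notes to the flow diagram and section 11.2 end collection 30 days after the last administration. The day of last dose is not given; assume day 7, 14 or 21.

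- Day 7: window closes on day 7 + 30 = 37, leaving 90 − 37 = 53 days uncovered (53/90 = 59%).
- Day 14: closes on day 44, leaving 46 days (51%).
- Day 21: closes on day 51, leaving 39 days (43%).

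If a drug continues after discharge and counts as the last administration, the window could run much longer. The flow diagram itself says adverse events are recorded at any time, and section 3 says throughout the study period.

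**6. What the ischaemic-only count leaves out.** If each patient is counted once, by first event, the difference between regimens in any stroke equals the ischaemic difference plus the haemorrhagic difference. Section 10.6 as defined shows only the first term. Two sets of assumed 90-day risks, chosen to illustrate and not taken from the protocol:

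- Regimen A 4.5% ischaemic and 0.2% haemorrhagic, regimen B 3.5% and 1.2%. Ischaemic only: 4.5 − 3.5 = 1.0 point in favour of B. Any stroke: 4.5 + 0.2 = 4.7% against 3.5 + 1.2 = 4.7%, no difference.
- Both 4.0% ischaemic, with 0.2% and 1.2% haemorrhagic. Ischaemic only: no difference. Any stroke: 4.2% against 5.2%.

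In the first set an any-stroke rate alone would also hide the contrast, so the types need separate rows.

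**The case against.** The best defence is that the criteria say what a medical institution diagnoses and the note says how the registry learns of it. The institution can do the imaging, so the absence of scheduled imaging in a non-interventional registry is not in itself a contradiction. That reading is reasonable, but the protocol does not state it, and nothing tells a site what to do when imaging status is unknown. It is also fair that ischaemic recurrence is a legitimate outcome in an ischaemic stroke registry; the difficulty is the name, and the lack of a haemorrhagic counterpart.

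Three stronger readings are tempting and are not supported:

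- A reader might infer that haemorrhagic strokes after discharge enter no endpoint. They can enter the primary and secondary mRS endpoints, including death, and within the AE window they are adverse events, serious if fatal or leading to hospitalisation.
- A reader might infer that antithrombotic regimens will look safer than they are. Recurrence is exploratory and not a safety parameter, the primary endpoint reflects net functional outcome, and no rates are given.
- A reader might infer that enrollees with an earlier stroke and an old infarct would be counted in bulk as recurrences. The 90-day horizon and the dated question make that unlikely in practice.

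**Conclusion.** The point holds as a clarification of one exploratory endpoint. The label is wider than the definition, the imaging criterion does not match the stated source, and onset after the index stroke is implied but not written. Haemorrhagic stroke after discharge can surface in several records but has no dedicated endpoint and no planned between-group comparison, so the recurrence comparison could be one-sided where regimens differ in antithrombotic content. The size and direction of any bias cannot be derived from the protocol. The AE-gap figures rest on assumed last-dose days, and the risk examples show a mechanism only. The change is worth making because it is cheap and because stroke type cannot be supplied reliably after data collection.

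**What to change.** In section 7.3, at Visits 4 and 5, define recurrence as a new stroke with onset after the index event, diagnosed by a medical institution as reported by the patient or family. Record type (ischaemic, haemorrhagic, unknown), date and whether imaging was reported. Use imaging to classify an event as confirmed or reported, and not as a condition for counting it. In section 10.6, report ischaemic and haemorrhagic stroke separately alongside any stroke. Reconcile the different statements of the AE collection period in the flow diagram, its notes, section 3 and section 11.2.

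The cost is one or two extra eCRF fields within a question already asked, plus protocol wording. Some telephone reports will have type unknown, and that share should be shown in the table.

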**Visit 5 (360 ± 28 days after administration, telephone visit)**

- mRS score
- EQ-5D scale
- Collect medical expenses

The patient's medical expenses from visit 4 to visit 5 should be recorded. (AIS related medical expense, not including the medical expenses for other diseases), including direct medical cost (including the dug expense, examination expense, laboratory test expense, diagnosis and treatment expense, nursing expense and bed expense due to outpatient service / emergency service / hospitalization) as well as direct non-medical cost (including transportation expense, nutrition expense, family accompanying expense and the expense of auxiliary devices). The above expenses are obtained through the inquiry from the patient and (or) family. Where the expense list cannot be provided, the estimate value verbally given prevails.

• Recurrence

The patient should be inquired about the recurrence, and the date of recurrence and whether the recurrence leads to inpatient treatment should be recorded.

Note: whether the disease recurs is based on the diagnosis of the medical institution verbally told by the patient or his/her cerebral infarction.

The stroke recurrence is defined as: 1) in conformity with the diagnosis criteria of ischemic cerebral stroke; 2) the history of past stroke with clear symptom; 3) infarction foci at different periods verified by cranial CT/MRI[13].

• Survival status

The patients should be inquired about the survival status, and as for the dead patients, it is necessary to record the date and reason of death.

• Re-admission

The patient should be asked whether he/she is re-admitted as well as the frequency and reasons of admission

- Study completed / ending page

**8.2 Safety evaluation**

The safety indexes in this study include:

1. Incidence rate of symptomatic intracranial hemorrhage transformation during the hospital stay
2. Adverse events
3. Vital Signs
4. Laboratory tests (blood routine test, blood glucose, blood lipids, liver and renal functions, myocardial enzymes, serum electrolytes, and coagulation function)
5. ECG examination

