# Study flow diagram

| **Phase** | **Baseline phase** | **Treatment phase** | | **Follow-up period** | |
| --- | --- | --- | --- | --- | --- |
| Visit | V1 | V2[a](#bookmark) | V3 | V4  (Outpatient or  telephone visit) | V5  (telephone visit) |
| Days | At admission  Day 0 | 7 ± 2 days after administration | At discharge | 90±14 days after administration | 360±28 days after administration |
| Signing informed consent forms | × |  |  |  |  |
| Inclusion / exclusion criteria | × |  |  |  |  |
| Demographic materials and medical insurance type | × |  |  |  |  |
| Visit delay and visits accepted by emergency | × |  |  |  |  |
| Past medical history and risk factors^b^ | × |  |  |  |  |
| Onset and admission^d^ | × |  |  |  |  |
| Glasgow coma score | × |  | × |  |  |
| NIHSS score | × | × | × |  |  |
| mRS score | × |  | × | × | × |
| EQ-5D scale | × |  | × | × | × |
| MMSE scale ^e^ |  |  |  | × |  |
| TOAST classification |  |  | × |  |  |
| Vital Signs^f^ | × | × | × |  |  |
| ECG examination | × |  | × |  |  |
| Laboratory examination^g^ | × |  | × |  |  |
| Imaging examination | × |  |  |  |  |
| Treatment regimen^h^ |  |  | × |  |  |
| Combined medications | × | × | × |  |  |
| Adverse events^i^  Special attention should be paid to the symptomatic intracranial hemorrhagic transformation | At any time | | | | |
| Medical expenses^j^ |  |  | × | × | × |
| Recurrence, survival status and re-admission |  |  |  | × | × |

Note:

1. At visit 2, if the patient is discharged, please directly perform the evaluation related with visit 3.
2. The visit delay, visits accepted by emergency and AIS risk factors are the items that can be evaluated.
3. Past medical history includes: stroke, hypertension, diabetes, dyslipidemia, coronary heart disease, atrial fibrillation, carotid plaques, and history of tumor.
4. Onset and conditions at admission: stroke occurrence time, and main symptoms
5. MMSE scale is only applicable to the patients that receive follow-up visits at 90±14 days after the initiation of administration.
6. The vital signs include body temperature, pulse, respiration and blood pressure. The changes in body temperature 1 day and 24 hours after the onset need to be collected at visit 1.
7. Laboratory tests include: blood routine test, blood glucose, blood lipids, liver and renal functions, myocardial enzymes, serum electrolytes, and coagulation function.

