8. The therapeutic regimen refers to AIS specific treatment, and the non-specific treatment needs to be recorded in the combined medication page.
9. The collection of adverse events starts from the signing of informed consent form to 30 days after the initiation of the last administration.
10. The medical expenses refer to the direct costs, including the direct medical costs and and direct non-medical costs. At discharge visit, the direct medical costs are acquired through the expense detailed list when the patient is discharged, and the direct non-medical costs (including the transportation expense, nutrition expense and family accompany expenses) are acquired through the inquiry of the patient or his/her family.

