# 3 Overview of study design

This was a registered, prospective, multi-center clinical study. The study was planned to included 10, 000 patients with acute ischemic stroke (AIS) and record treatment regimens, treatment outcomes and medical expenses during hospitalization in real clinical practice. This study was to collect patients' data through a electronic data capture system (EDC).

According to the recommendations for treatment and follow-up observations in acute phase in the "Guidelines on diagnosis and treatment of acute ischemic stroke in China 2014 (Draft)", the patients with stroke were planed to receive 5 visits, which occurred at admission (baseline assessment, visit 1), 7 days ± 2 days after medication (visit 2), at discharge (visit 3), 90 days ± 14 days after medication (visit 4, outpatient service or telephone follow-up), and 360 days ± 28 days after medication (visits 5, telephone follow-up), respectively. As for the specifics, refer to [Study Flow Chart](#bookmark14).

In the baseline phase, the investigators should verify the inclusion/exclusion criteria, obtain the patients' informed consent, and try to collect the demographic information, past history, onset and admission conditions, and vital signs of the patients; and collect the following data of clinical examination: ECG, laboratory tests (blood routine, blood glucose, blood lipids, hepatic and renal functions, cardiac enzymes, serum electrolytes, coagulation) and imaging findings, and assess Glasgow Coma Scale, NIHSS score, mRS score and EQ-5D Scale. Seven days ± 2 days after medication, the vital signs of the patients were recorded and the NIHSS scores were accessed again. At discharge, the treatment regimen, vital signs, ECG and above laboratory tests results were recorded during hospitalization, and the Glasgow Coma Scale, NIHSS score, mRS score and EQ-5D scale were accessed, and the medical expenses during hospitalization was also collected. On 90 ± 14 days after medication, the recurrence of stroke, survival conditions and re-admissions were collected; the medical expense until this visits since discharge was recorded; and the mRS score, EQ-5D scale and MMSE scale (only applicable for the patients visiting the hospital) were accessed. On 360 days ± 28 days after medication, another telephone follow-up was given again, to ask the patient's health status, access mRS score, EQ-5D scale, and collect medical expenses.

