**10.4 Safety Analyses**

Descriptive statistics are mainly used for safety analysis. The incidences of symptomatic intracranial hemorrhage transformation between the groups are described statistically and compared by using the test of χ^2^ or the exact test of Fisher.

According to the relevant regulations of the state, the SAE incidence of the relevant product of the sponsor shall be described.

The vital signs and the laboratory test mesasurements shall be statistically described and compared by using Student's paired t-test and the Wilcoxon signed rank test befoer and after the baseline. The changes of laboratory test results and the ECC indexes are described with cross tabulations before and after the assessment.

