**Adverse Event (AE)**

An adverse event (AE) refers to any untoward medical event experienced by patients or subjects after taking the drug, but the event does not necessarily have a causal relationship with the treatment. Therefore, an adverse event (AE) can be any untoward and unexpected signs (including abnormal investigation findings), symptoms or disease that are temporally related to the used (investigational) drug regardless of whether the event is related to the drug.

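### Symptomatic haemorrhagic transformation is compared between regimens, but repeat scans have no data field, so unequal rescanning of deteriorating patients could bias the comparison without showing in the data

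*Protocol*

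**What the plan says.** Section 8.2 names as the first safety index "Incidence rate of symptomatic intracranial hemorrhage transformation during the hospital stay". Section 10.4 then states: "The incidences of symptomatic intracranial hemorrhage transformation between the groups are described statistically and compared", by chi-square or Fisher's exact test. Section 5 leaves the choice of regimen to the treating doctor, so the groups are not randomised.

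Haemorrhage at entry is an exclusion (section 4.2: "Cranial CT/MRI can display the presence of cerebral hemorrhage"). The imaging item, "Imaging examination (Cranial CT/MRI and vascular examination", appears in the Visit 1 list of section 7.1. The study flow diagram also marks imaging at Visit 1 alone. The Visit 2 and Visit 3 lists in section 7.2 contain no imaging item.

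The event has another route into the database. The adverse-event row of the flow diagram applies throughout the study and adds: "Special attention should be paid to the symptomatic intracranial hemorrhagic transformation". Section 11.1 defines an adverse event to include "any untoward and unexpected signs (including abnormal investigation findings), symptoms or disease". A note to the flow diagram sets the window: "The collection of adverse events starts from the signing of informed consent form to 30 days after the initiation of the last administration".

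**The concern.** Because haemorrhage on the entry scan excludes a patient, a transformation can be confirmed by imaging only on a later scan. Whether that scan is done is left to routine practice, and the protocol has no item recording that it was done, why, or what it showed.

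An adverse-event report is a record of positives. Among patients who worsen or die in hospital with no report of bleeding, some were rescanned and found clear and others were never rescanned. The database does not separate them. By default the second kind appears event-free, unless the investigator reports the event on clinical grounds.

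At stake is a between-regimen safety comparison. Regimens run from thrombolysis to herbal medicines, and the intensity of observation could differ with regimen, severity or site. A regimen whose deteriorating patients are rescanned more often would then show more bleeds at the same true risk. A statistical analysis plan can add a definition or a sensitivity analysis, but it cannot recover scan status that was never collected.

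**Working it through.** **1. What is recorded, set side by side**

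| Item | Visit 1 | Visit 2 | Visit 3 (discharge) |
|---|---|---|---|
| Imaging | yes | no | no |
| NIHSS | yes | yes | yes |
| Glasgow coma score (flow diagram) | yes | no | yes |
| Adverse events | yes | yes | yes |

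No place in the protocol defines the event or says how a patient who worsens or dies without a repeat scan is classified. By contrast, stroke recurrence, an exploratory outcome, has a three-part definition in section 7.3 that includes CT/MRI verification. NIHSS is repeated during the stay (section 3: "Seven days ± 2 days after medication, the vital signs of the patients were recorded and the NIHSS scores were accessed again"), but nothing links a worse score to a scan or to this event.

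**2. Which patients are affected**

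- Bleed found on a routine-care scan: reportable as an adverse event, so captured.
- Stable and never rescanned: no symptomatic event, so scoring no event is right.
- Worsened or died, rescanned and clear: no event, correctly.
- Worsened or died, not rescanned: true status unknown, and indistinguishable from the previous line.

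The problem lies in the last two lines only.

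**3. Size, as an illustration**

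The protocol states no event rate, scanning rate or power for this endpoint, so there is no figure to reproduce. Taken from the protocol: two-sided 5% test (abstract, statistical methods). Assumed: the same true risk *t* in two groups, *n* per group, a share *s* of true bleeds scanned in each group, and a bleed counted only if scanned.

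- Observed risk: p = t × s.
- Null standard error: SE0 = √[2 p̄(1 − p̄)/n], with p̄ = (p1 + p2)/2.
- Alternative standard error: SE1 = √{[p1(1 − p1) + p2(1 − p2)]/n}.
- Rejection probability: Φ[(d − 1.96 SE0)/SE1] + Φ[(−d − 1.96 SE0)/SE1], with d = p1 − p2.

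With t = 4% and n = 1,000 per group:

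- *90% v 80% scanned.* p1 = 0.04 × 0.90 = 0.036; p2 = 0.04 × 0.80 = 0.032; d = 0.004; SE0 ≈ SE1 ≈ 0.0081. Rejection = Φ(−1.47) + Φ(−2.45) ≈ 0.071 + 0.007 = 0.078, about 8%.
- *90% v 50% scanned.* p1 = 0.036; p2 = 0.020; d = 0.016; SE0 ≈ SE1 ≈ 0.0074. Rejection = Φ(0.21) + Φ(−4.13) ≈ 0.58.

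Other cases by the same formula:

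| True risk | Scanned | Observed risks | n per group | False rejection |
|---|---|---|---|---|
| 4% | 90% v 80% | 3.6% v 3.2% | 300 | 6% |
| 4% | 90% v 50% | 3.6% v 2.0% | 300 | 22% |
| 3% | 90% v 75% | 2.7% v 2.25% | 1,000 | 10% |
| 3% | 90% v 60% | 2.7% v 1.8% | 1,000 | 27% |
| 3% | 90% v 60% | 2.7% v 1.8% | 2,500 | 57% |

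With equal scanning, p1/p2 = (t × s)/(t × s) = 1. Both rates are too low by the factor *s*, but the ratio is undistorted and the test keeps its nominal 5%.

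**The case against.** The strongest reply is that the protocol does collect this event. It is the only adverse event singled out for special attention, abnormal investigation findings count as adverse events, the window covers the hospital stay, and section 14.5 has monitors checking adverse-event records against source. All of this stands for bleeds that are found. It does not show who was looked at. In addition, sections 11 and 11.2 require a written report to the sponsor within 24 hours only for patients on the sponsor's product. General collection covers every patient, but this extra duty falls unevenly across regimens.

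Deterioration is also partly visible through the scheduled NIHSS and Glasgow scores and through serious adverse events, and Visit 3 collects imaging expense. These help, but none says whether a repeat cranial scan was done, when, or with what result.

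The lack of scheduled repeat imaging suits a non-interventional registry and is not a fault. A case definition and sensitivity analyses may also sit in a statistical analysis plan. The missing data field remains.

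A reader might infer more than the protocol supports:

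- *That every unscanned patient is misclassified.* Stable patients who are not rescanned have no symptomatic event.
- *That the plan counts unscanned deterioration as event-free.* There is no classification rule. That is only the default when nothing is reported.
- *That a false difference is likely.* The high probabilities above need scanning gaps of 30 to 40 percentage points, and the protocol supports no gap of any particular size.

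**Conclusion.** The point holds as a gap in data collection. A safety endpoint that needs a later scan is tested between physician-chosen regimens, and the protocol has no field showing which deteriorating patients had that scan. Differential detection is possible and, if present, could be neither seen nor corrected.

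Its size cannot be established from the protocol. Under the assumptions shown (true risk 4% in both groups, 1,000 per group, bleeds counted only if scanned), the false-rejection probability runs from the nominal 5% with equal scanning, through about 8% at 90% v 80%, to 58% at 90% v 50%. For a given gap it grows with group size, which matters in a registry of 10,000. The change is worth making because it is cheap and must be made while data are being collected.

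**What to change.** - **Study flow diagram and the Visit 2 and Visit 3 lists (section 7.2):** record the date, reason and result (new haemorrhage yes/no) of any repeat cranial CT/MRI done in routine care. No scan is added for the study.
- **Section 8.2:** define the event for analysis as new haemorrhage on such a scan with neurological worsening documented by the investigator at the time. Do not tie it to the scheduled NIHSS, which is taken only at admission, day 7 ± 2 and discharge and can miss a bleed or death in between. Flag in-hospital deterioration or death without a repeat scan as not assessable.
- **Section 10.4:** report by regimen the share of all patients, and of deteriorating patients, who were rescanned. Add two sensitivity comparisons: one excluding not-assessable patients and one counting them as events. Label the second as a worst-case bound, because it mixes in deaths and deteriorations from other causes and could swamp a rare event.

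The cost is a few eCRF fields filled from existing records and short wording changes in the places named. The downside is slightly more data entry.
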